#### Ethics and dissemination

2.1.12

The study protocol is in accordance with and was based on the Helsinki Declaration. Ethics approval was obtained from the Medical Bioethics Committee of the Centre of Postgraduate Medical University (Decision No. 56/PB/2020). The study has been registered at Clinicaltrials.gov, registration number NCT04377412. Participation in the study is voluntary and anonymous. Participants consent to the study by filling a web-based survey and clicking the submit button at the end. Before beginning they are informed that they can withdraw at any time and none of the information will be stored in the database. Participants may provide their personal information for participation in future research, but this information will not be linked with the data provided in this study.

The results of the study will be presented at local, national and international conferences related to mental health, pregnancy and COVID-19. Data will be published in peer-reviewed journals. The main findings of the study will also be shared and disseminated to researchers, health service providers, healthcare professionals and the public, especially pregnant women through all forms of media and communication.

## Results

3

Web-based recruitment is not free of problems, but it is time-efficient and allows for fast data collection in cross-national settings. Typical survey procedures require months of preparation, and realization is not free of obstacles. Despite the potential problems, web-based surveys have proven to be useful in many types of projects,^[37]^ including assessment of mental health as well as other aspects of pregnancy, for example, nutritional habits.^[38]^ In this study data collection procedures are designed to maintain the highest degree of cross-country comparability.

Web-based recruiting for health research has proven to be cost-effective and efficient.^[39]^ At current times with the COVID-19 pandemic, because of limited resources, and social distancing restrictions, performing a mental health study involving pregnant women on a large international scale cannot be safely conducted without involving the social-media.

A web-based survey can be prone to several types of bias, such as non-response bias, response bias, selection bias, recall bias, and volunteer bias.^[40]^ Although the medium used to propagate the survey is available both in developed and underdeveloped countries, there is a risk that our survey will reach more women of a higher socioeconomic status and from larger agglomerations. To some extent, we could control this bias using historical data collected by conventional methods. In our study, additionally, bias will be accounted for by planning the campaigns for the dissemination of the survey to reach populations in various settings. Response-bias, on the other hand, is a situation when there is a systematic distortion in the way respondents answer the questions. This kind of bias is mainly a problem in surveys that investigate socially unacceptable/embarrassing behavior, that is, alcohol consumption or illegal drug use. Although this is not the case, there is a risk that pregnant women are particularly worried about the COVID-19 pandemic and will be more likely to respond to the advertisement of a survey assessing mental health related to the COVID-19 pandemic. This type of bias is also defined as recall bias, which is often the case in medical surveys where respondents who are prone to a specific sickness, are sick, or are more interested in the disease, are more likely to respond to a survey.^[41]^ For this reason, we will collect background information regarding mental health problems and previous treatments to distinguish such responses. We expect a higher incidence in difficulties with coping with the COVID-19 pandemic in women with a previously diagnosed mental health problem. It has been described that the experience of having the studied condition encourages an ’effort after meaning.’ The participant in such a case has already gone over his/her life history to understand why he/she has become ill. This clearly predisposes to recall bias.^[41]^ Again, this is not the case in our study. Volunteer bias would have occurred if there is a systematic difference between those who volunteer to be part of the study (completed the survey) and the population. In this case, we use a convenience sampling method, which involves sampling participants who are available to be approached at the time of recruitment. Also, we are approaching a specific part of the population – pregnant women. If there were a significant difference between those patients selected for the survey and those who are not, this would result in a sample that is not representative of the population. Convenience sampling is a proven, efficient, cost-effective method of recruitment for a web-based survey.^[42]^ The study aims to assess differences between countries resulting from the COVID19 pandemic. It will be hard to assess if the presented views will reflect the views of the general population of pregnant women in specific countries. This can be accounted for by analyzing the spread of the demographic and socioeconomic factors in the studied populations. The strength of the study is that we are targeting unselected pregnant women.

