#### Sample size

2.1.9

The estimated sample size is 500 for each country. This has been calculated using the CinCalc.com sample size calculator.^[25]^ Results of GAD-7 for the general population vary between 4,75 (+/−4.76) to 5,7 (+/− 4.9).^[20,26]^ For PHQ-9, the scores vary from 3,0 (+/−4,3; for population in age of 30–39) to 5,2 (+/− 5.06).^[26,27]^ To detect a 20% difference separately in anxiety (GAD-7 scale) and depression levels (PHQ-9 scale) between the studied countries using a power of 80% and a margin error of 0.05,^[25]^ the calculated sample size for GAD-7 is 394 in every single country and for PHQ-9 calculated sample size is 372 in every single country. Values yielding higher sample sizes will be used. This sample size will allow us to compare reported anxiety and depression levels among pregnant women in different countries around the world affected by the pandemic.

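### Over-response by worried women is self-selection on the outcome, but the article calls it recall bias and relies on demographic adjustment, which would leave country contrasts biased if that selection differs between countries

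*Protocol article*

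**What the plan says.** The Introduction gives the primary aim as comparing anxiety and depression scores of pregnant women between countries.

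The Results section (3) discusses bias in these steps:

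- Women who are particularly worried about the pandemic "will be more likely to respond to the advertisement of a survey assessing mental health related to the COVID-19 pandemic".
- It labels this recall bias. In response, the survey collects mental-health problems and previous treatment, so that such responses can be told apart.
- It then describes recall bias in the usual sense, where ill people search their past for an explanation, and says this does not apply here.
- It defines volunteer bias, states that "we use a convenience sampling method", and concedes that representativeness for a country's pregnant women will be hard to judge. The next sentence reads "This can be accounted for by analyzing the spread of the demographic and socioeconomic factors in the studied populations".
- It closes with "The strength of the study is that we are targeting unselected pregnant women".

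Statistical analysis (2.1.11) reweights to external distributions of age, place of residence and education. If those data are lacking, propensity score matching and regression are to balance demographic distributions. Measurement invariance analysis and structural equation modelling follow, with exploratory regressions on medical, sociodemographic and pandemic-related variables.

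**The concern.** Whether a woman answers because she is worried is a matter of who enters the sample, not of how she remembers past events. Since worry is close to what GAD-7 and PHQ-9 measure, response depends on the outcome itself. The recall-bias label points the reader to the wrong remedy. The later definition of volunteer bias, which does fit, is never linked to the worried women.

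Demographic reweighting restores the mix of age, residence and education. It does not correct over-response of high scorers within a cell of those variables. Invariance analysis asks whether items work alike among those who answered, and says nothing about who answered.

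At stake is the primary country contrast. Data collection (2.1.10) describes advertising campaigns, invitations through closed groups, several languages and recruitment starting at different times by region. It is plausible that the pull on worried women then differs between countries. If it does, part of an observed difference is an artefact, and a larger sample does not reduce it.

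**Working it through.** **1. The plan's own figures.** Section 2.1.9 aims "To detect a 20% difference separately in anxiety (GAD-7 scale) and depression levels (PHQ-9 scale) between the studied countries". With two-sided 0.05 and 80% power, n per country = 2(1.960 + 0.842)² SD²/δ² = 15.70 × SD²/δ².

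- GAD-7: mean 4.75, SD 4.76, δ = 0.20 × 4.75 = 0.95. n = 15.70 × 22.66/0.9025 = 394.1 (stated: 394).
- PHQ-9: mean 5.2, SD 5.06, δ = 0.20 × 5.2 = 1.04. n = 15.70 × 25.60/1.0816 = 371.6 (stated: 372).

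So the yardsticks are 0.95 and 1.04 points.

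**2. Shift caused by selection.** Let k be the response rate of women at or above a cut-off divided by that of women below it. The documents give no value, so k is an assumption, shown from 1.25 to 3. With P the true proportion at or above the cut-off, and D the mean above minus the mean below,

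shift in mean = D × P(1 − P)(k − 1) / [1 + P(k − 1)].

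A beta-binomial on 0–21 matched to mean 4.75 and SD 4.76 gives P = 0.297, D = 8.89 at cut-off 7 (the pregnancy cut-off in 2.1.5) and P = 0.173, D = 10.24 at cut-off 10. For example, k = 2 at cut-off 7: 8.89 × 0.297 × 0.703/1.297 = 1.43.

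False GAD-7 difference, no true difference, k as shown in one country and 1 in the other:

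| k | cut-off 7 | cut-off 10 |
|---|---|---|
| 1.25 | 0.43 | 0.35 |
| 1.5 | 0.81 | 0.67 |
| 2 | 1.43 | 1.25 |
| 3 | 2.33 | 2.17 |

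Setting the shift to 0.95 gives k = 1 + 0.95/[D·P(1 − P) − 0.95·P]: about 1.60 at cut-off 7 and 1.73 at cut-off 10. For PHQ-9 (P = 0.189, D = 10.58, cut-off 10), 1.04 points is reached at about 1.73.

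**3. Dependence on the model.** A truncated negative binomial refitted to the same mean and SD needs 1.62 (cut-off 7) and 1.75 (cut-off 10). One truncated at 21 without refitting (mean 4.54, SD 4.27, 13% scoring 10 or more) gives shifts of 0.53, 1.00 and 1.79 for k = 1.5, 2 and 3 at cut-off 10, so it needs k just under 2.

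**4. Selection in both countries.** For k = 2 against 1.5, the difference is 0.62 at cut-off 7 and 0.57 at cut-off 10 (beta-binomial), or 1.00 − 0.53 = 0.47 in the unrefitted model. Equal k with equal true distributions gives 0. Equal k of 1.5 or 2 with a true difference of 0.95 gives 0.98 to 0.99, so common selection distorts the contrast very little.

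**5. Chance of a false significant result.** At 500 per country the standard error is 4.76 × √(2/500) = 0.301. At cut-off 7, comparing two means, a false significant difference occurs with probability about 30% for k = 1.25 against 1, 77% for 1.5 against 1, and 54% for 2 against 1.5.

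**6. What demographic balancing removes.** In a simulation, women were post-stratified in deciles of a demographic score that explains 0, 5, 10 or 20% of the variance of the latent anxiety score (assumed values). Bias left at cut-off 7:

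| variance explained | k = 1.5 (raw 0.81) | k = 2 (raw about 1.43) |
|---|---|---|
| 0% | 0.81 | 1.43 |
| 5% | 0.78 | 1.37 |
| 10% | 0.74 | 1.30 |
| 20% | 0.67 | 1.16 |

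Even at 20%, less than a fifth of the bias is removed.

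**The case against.** A reader might infer more than the article says in four respects.

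- *That it claims its respondents are unselected.* The sentence speaks of whom the study targets. It may mean recruitment not restricted by clinic, risk or diagnosis, which fits the inclusion criteria in 2.1.8. The same section admits convenience sampling and doubtful representativeness. The sentence is ambiguous rather than a plain denial of selection.
- *That it waves the risk away.* The remark that recall bias does not apply follows the description of genuine recall distortion. It does not deny that worried women respond more, and the article offers mental-health history as its response to that.
- *That the planned adjustment is purely demographic.* The regressions in 2.1.11 include medical and pandemic-related variables, and the Results section also mentions campaigns aimed at varied settings and historical data. These may reduce the bias. They do not remove it: a previous diagnosis is only a proxy for the current score, and the regressions are described as exploring associations.
- *That the country contrast is shown to be biased.* It is not. The response ratios are assumed, a ratio above 1 in only one country is the extreme case, and the article expects over-response in general, which cancels if it is equal and the true distributions are equal.

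Detailed sensitivity analyses may also stand in an analysis plan that is not shown, so their absence from an article is not the fault. What stands is what the article states: the wrong name for the mechanism, and the claim that demographic and socioeconomic factors can account for doubtful representativeness.

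**Conclusion.** The point holds in this form: the article foresees self-selection on the primary outcome, misnames it, and credits demographic adjustment with more than it can do. The country contrast is biased only if the selection differs between countries, which the recruitment methods make plausible but which nothing in the documents quantifies.

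As an illustration, a ratio of about 1.6 to 2 in one country against 1 in the other reproduces the 0.95-point GAD-7 design difference or exceeds it, and 2 against 1.5 gives about 0.5 to 0.6 points. These figures rest on the assumed ratios, on the planning mean and SD (quoted for the general population), on the chosen cut-off and on the shape of the score distribution. The direction does not depend on the model; the exact thresholds do. The point should be corrected, but the design need not change.

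**What to change.** In the Results section:

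- Call the expected over-response of worried women self-selection on the outcome, not recall bias.
- Replace the sentence saying that representativeness can be accounted for with a statement that demographic adjustment does not remove this selection.
- Reword the closing sentence to say that recruitment is not restricted by clinic, risk or diagnosis.
- State that conclusions apply to women who respond through social media.

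In Statistical analysis (2.1.11), add two sensitivity analyses for the primary country contrasts, both on data already collected:

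- a tipping-point analysis over a range of response ratios that differ between the two countries, reporting how unequal they must be to remove the observed difference;
- the contrast adjusted for mental-health history.

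The cost is a more modest claim and slightly more analysis, with no new data. The history-adjusted contrast should be read as secondary, because rates of diagnosis may themselves differ between countries.

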
## Discussion

4

### Mental health impact

4.1

As a result of COVID-19 related mortality and morbidity, the rapid spread of the virus worldwide, WHO (World Health Organization) announced a pandemic state on 12 March 2020. As a result of the announcement, but also prior to the announcement, governments worldwide implemented measures to avoid further spread of the virus and reduce the number of causalities.^[43]^ Because of the pandemic, many essential services that usually make life easier, like banking, shopping facilities, all kinds of services, including medical, childcare, schools, sports and entertainment are unavailable due to new regulations. Many people are asking themselves questions such as: “How long will all this last?”, ‘How will it impact my life in the long-term?”, “Will I have a job when this is over?”, “Will I have an employer to return to?”, “Will all my family members survive?” and many more. Isolation and social distancing are important risk factors of mental health.^[44–46]^

### Pregnant women and their unborn babies

4.2

Fetal well-being is one of the main maternal concerns. Although the possibility of vertical transmission has not been confirmed with concrete evidence, women may feel worried about such risk or infection of the infant in the peripartum period. Pregnancy is also the time of increased medical observation, which is difficult to facilitate during the pandemic.^[47]^ The difficulty in accessing professional medical help may also be a source of anxiety for pregnant women.^[48]^ Besides, pregnant women may feel insecure about exposure risk to the coronavirus when accessing medical facilities.

### Existing children and family members

4.3

Since schools have been closed, the 24-hour presence of children at home is an additional source of stress because of the additional time dedicated to looking after them, the lack of physical/outdoor activities and the need to provide home-schooling. Financial problems and newfound duties related to family care can potentially lead to misunderstandings between family members. The support of the partner has a significant influence on maternal well-being and therefore single mothers may be more prone to anxiety.^[49]^

### Societal impact

4.4

The COVID 19 pandemic has resulted in increased fear and uncertainty. This in turn may lead to negative societal behaviors. This may include behaviors aimed at regaining control of the situation, such as clearing shelves at supermarkets resulting in temporary shortages of food or other essentials such as toilet paper.^[50]^ More and more countries are implementing mass quarantines. The experience of isolation, fear of being trapped and rumors spread on social media can all result in growing anxiety and social panic.^[50]^ Other aspects of social life are being severely affected as well, such as family gatherings, participation in holidays, religious celebrations, births, funerals and many more. All of these can lead to growing anxiety and depression.^[51]^ Another important social aspect is the fear of blame, guilt and stigmatization related to being infected with COVID-19. Infected people may become a target of discrimination. There have been documented incidents of suicide due to guilt related to being infected as well as to social media bullying of medical professionals.^[52,53]^

### Economic impact

4.5

The COVID-19 pandemic has affected the job market. Salaries have often been reduced and many people have lost their jobs leading to difficulties in paying bills and loans, and problems with daily survival costs. Measures to contain the virus directly influence economy. In China where the outbreak struck first, production fell by 13.5% and some sectors have collapsed completely, such as car sales by 92% and restaurant sales by 95%. The predicted decrease of the US economy in the second quarter of 2020 is 24% as a result of the COVID-19 pandemic.^[54]^ More than a decade ago the world suffered an economic crisis similar to the one we are expecting to happen now. That global financial crisis resulted in declining mental health worldwide with a rising number of suicides, alcohol and drug related deaths.^[54]^ The intricate vine of dependencies between the safety of all people, economy, health and political systems shows how vulnerable we have all become during these difficult times.

## Conclusion

5

The COVID-19 pandemic has shown us that in an extreme environment mental health is a major public issue. The crisis that we are facing now, if appropriately managed, may become an opportunity for a global social transformation of perceptions, and interventions are needed to address mental health.^[55]^ We hope that our study, with its international reach, issues to be addressed and data to be gathered, will play a role in this process.
